### Data analysis

#### Sample size

This study is the first to investigate the effects of KE in patients with SSD and BD and is designed as a pilot and feasibility study, precluding a formal sample size calculation based on pre-existing data. Because of the lack of consensus on sample size calculation in pilot/feasibility studies, we have relied on existing literature as a basis for our decision. Following Julious' recommendations [98], we have chosen a sample size of 12 subjects per group. Therefore, a total of 24 patients with either SSD (n = 12) or BD (n = 12) will be included in the study. If a participant drops out, efforts will be made to include a replacement.

### *Statistical analysis*

Comparisons regarding all outcome measures within patients (dGK condition compared with control drink condition) are performed using paired-samples *t* tests for normally distributed data (or Wilcoxon signed-rank test if parametric assumptions are not met). Group-level effects will be analyzed using a linear mixed effects model, with adjustment for confounding factors. A significance level of ≤0.05 will be used. Given the exploratory nature of this pilot study, no imputation analysis will be conducted in the case of missing data (except for missing EEG channels) and no correction for multiple testing will be applied.

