##### Immune, oxidative stress, and metabolic blood parameters

Participants may opt out of blood sampling. For those who consent, a venous cannula is inserted into a forearm vein at the start of each session to facilitate sequential blood draws without repeated venipunctures. Blood is collected at the following time points: before drink ingestion (baseline, T0), at 20-min intervals during the first hour after ingestion (T1–T3), and at 30-min intervals thereafter (T4–T7), with a maximum of 8 blood draws and 123 mL per session. At each timepoint, ∼15 mL of blood is drawn and distributed over 5 tubes: 1 for serum (5 mL), 1 for plasma isolation using heparin (5 mL), and 3 EDTA tubes, used, respectively, for ketone body determination (1 mL), acylcarnitine profiles (1 mL), and remaining plasma. For ketone body determination, the EDTA sample is immediately mixed (1:1 ratio) with perchloric acid and kept on ice to prevent conversion into and evaporation of acetone. In addition, a 3 mL Tempus Blood RNA tube is collected at 1 h (T3) after drink ingestion, for gene expression analysis using the metabolic and immune nCounter gene expression panels from Nanostring. Following collection, all blood samples are handled in accordance with standardized laboratory protocols. Processed supernatants and aliquots are subsequently stored at −80°C until further analysis.

Immune, oxidative stress, and metabolic markers are determined in serum, plasma, and deproteinized blood. Markers are chosen according to prior research findings. Inflammatory markers include IL-6 and IL-10, measured in plasma, and high-sensitivity C-reactive protein (and soluble intercellular adhesion molecule-1 in serum) [13,20,[85], [86], [87]]. Oxidative stress markers include glutathione S-transferase and superoxide dismutase and key enzymes in ROS regulation [88,89]. Metabolic markers include glucose, ketone bodies (BHB and AcAc), and acylcarnitine profile [90,91].

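### The blanket rule of p≤0.05 with no multiplicity correction also covers two gene-expression panels and an acylcarnitine profile, where about 5% of true nulls are expected to be flagged

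*Protocol article*

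**What the plan says.** All of this is in the protocol article.

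- **Scope.** Under Statistical analysis, the paired t or Wilcoxon signed-rank tests apply to "Comparisons regarding all outcome measures within patients (dGK condition compared with control drink condition"). A linear mixed effects model is added for group-level effects.
- **Threshold.** "A significance level of ≤0.05 will be used".
- **Multiplicity.** "no correction for multiple testing will be applied", with the reason "Given the exploratory nature of this pilot study".
- **Gene expression.** The section Immune, oxidative stress, and metabolic blood parameters, one of the secondary outcome sections, plans a single RNA tube per session, one hour after the drink. Its stated purpose is "for gene expression analysis using the metabolic and immune nCounter gene expression panels from Nanostring".
- **Acylcarnitines.** In the same section: "Metabolic markers include glucose, ketone bodies (BHB and AcAc), and acylcarnitine profile".

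No class of outcome is exempted from the rule. The number of genes and the number of acylcarnitine species are not stated. Blood sampling is optional, PPI is the only primary outcome, and the mechanism work is described as exploratory under Aims and objectives.

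**The concern.** A pilot with one primary outcome and a short list of named secondary outcomes can reasonably report unadjusted p-values. A reader can count those outcomes and discount accordingly. A panel assay is different. It produces many p-values at once, and the usual report is the subset that crosses the threshold. If that threshold is an unadjusted 0.05, the length of the list depends partly on panel size, and nothing in the list separates effects of the drink from chance.

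This matters because exploring mechanisms is a stated aim, and the Discussion calls the breadth of outcomes a strength since it may inform later trials. RNA is taken once per session, so no second sample in that session can support a flagged gene. If the ketone ester has little effect on expression at 1 h, most or all of the flagged genes would be false leads.

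This is not a detail left to an analysis plan that is not shown. The article states a definite rule, and an analysis plan that followed it would carry the problem forward.

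**Working it through.** **Inputs from the article.** Per-test level α = 0.05 (sidedness not stated; two-sided assumed). Adjustment: none. Two gene panels, one RNA tube per session. Planned sample 12 + 12 = 24 patients, fewer for blood outcomes if some opt out. The article gives no number of tests and no error rate across tests, so there is no figure of its own to reproduce.

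**Assumed input.** m, the number of features with no true effect. One RNA time point means at least one paired comparison per gene.

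**Step 1: expected false flags = α × m.**

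| m (assumed) | Expected false flags | P(at least one) = 1 − 0.95^m, independent tests |
|---|---|---|
| 100 | 0.05 × 100 = 5 | 0.994 |
| 500 | 0.05 × 500 = 25 | >0.999 |
| 1,000 | 0.05 × 1,000 = 50 | >0.999 |

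**Step 2: how far the count can vary.** Correlation leaves the expected count unchanged but spreads the actual count. A simulation with one common factor, two-sided z tests and 4,000 runs, with ρ the correlation between test statistics, gave:

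| ρ | m = 500: median | m = 500: P(≥24) | m = 1,000: median | m = 1,000: P(≥24) |
|---|---|---|---|---|
| 0 | 25 | 0.60 | 50 | 1.00 |
| 0.3 | 16 | 0.34 | 32 | 0.72 |
| 0.5 | 9 | 0.26 | 18 | 0.43 |
| 0.7 | 3 | 0.23 | 6 | 0.30 |

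At m = 1,000 and ρ = 0.7, about 18% of runs had no false flag at all. An expected count of 24 needs 24 / 0.05 = 480 true nulls.

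**Step 3: contrast with the named blood markers.** There are nine: IL-6, IL-10, hsCRP, sICAM-1, glutathione S-transferase, superoxide dismutase, glucose, BHB and AcAc. With one test each and all nulls true, 0.05 × 9 = 0.45 false flags are expected, and P(at least one) = 1 − 0.95^9 = 0.37. A reader can allow for that. The difficulty lies in the panels and the profile.

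**Step 4: which kind of control is workable.** The smallest two-sided exact Wilcoxon p with 12 pairs (one diagnosis group) is 2 / 2^12 = 0.00049. Bonferroni over 500 tests needs 0.05 / 500 = 0.0001, so it could never reject there. Benjamini-Hochberg compares the k-th smallest p with k × q / m. With q = 0.10 and 1,000 genes the step is 0.0001 per rank, so five genes at the minimum p would pass (5 × 0.0001 = 0.0005 ≥ 0.00049). With all 24 pairs the minimum p is 1.2 × 10^-7, so this limit does not bind.

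**The case against.** The strongest defence is that the choice is disclosed and reasoned. The study is a pilot, PPI is the sole primary outcome, the mechanism work is labelled exploratory, and no confirmatory claim or decision is tied to a gene list. This stands for PPI and the individually named secondary outcomes, and nothing here asks for correction there. It does not cover the panels. An exploratory screen still has to show how much of its output is likely to be noise, and false-discovery-rate control is a standard tool for exactly that.

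A second defence is that the size of the problem is unknown because the panel sizes are not given. This also stands. A reader might infer that dozens of false mechanism signals are certain. The article does not support that: it needs roughly 480 or more true nulls, it would still be an expectation, and correlated genes can give far fewer.

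A reader might also infer that each serial blood marker will be tested at every draw. Seven post-drink tests would give up to 1 − 0.95^7 = 0.30 for at least one false positive per marker, if independent. But the article gives only sampling times ("with a maximum of 8 blood draws and 123 mL per session", of which the one at T0 precedes the drink). It does not say that each time point is tested, and how a curve is summarised is commonly left to the analysis plan. BHB and AcAc, moreover, should truly differ after a ketone drink. The serial curves are therefore no part of this point.

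**Conclusion.** The point holds for the two gene-expression panels and the acylcarnitine profile, and only for these. As written, the uncorrected 0.05 rule applies to them, and about 5% of their true nulls are expected to be flagged: 5 per 100, 25 per 500, 50 per 1,000. The 5% rate follows from the stated rule, given valid tests. The counts rest on assumed panel sizes, and the near-certainty of at least one false flag also rests on independence. The primary outcome is unaffected. What suffers is the mechanism results, which would be hard to interpret as a guide to the later trial. The rule should be changed, but it does not threaten the trial's main comparison.

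**What to change.** Limit the no-correction sentence to the primary outcome and the individually named secondary outcomes, labelled exploratory. For the metabolic panel, the immune panel and the acylcarnitine profile, do one of the following:

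- apply Benjamini-Hochberg control within each of the three families at a pre-stated level (for example 5–10%), and report the number of features tested; or
- report each family as a ranked list with effect estimates, marked as hypothesis-generating, with no significance claims.

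The second option may suit better if few patients consent to blood sampling, because the smallest attainable Wilcoxon p rises quickly as pairs are lost (2 / 2^8 = 0.0078 with eight pairs).

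The change takes a sentence or two and a standard routine. It needs no new samples, visits or patients and leaves the PPI analysis as it is. The downside is fewer nominally significant genes, and some real but weak effects will not pass the stricter threshold.

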### Data monitoring

#### Patient safety

This study utilizes well-established nutritional drinks with no known harmful side effects. Patients are clinically admitted to the department of psychiatry and are closely monitored by both the investigators and the clinical staff responsible for their treatment. In the highly unlikely event of an unexpected adverse effect, the procedures outlined in the study protocol will be followed. In accordance with Section 10, Subsection 4, of the WMO, the sponsor will suspend the study if there are sufficient grounds to believe that continuing the study may endanger the health or safety of the subjects.

#### Public disclosure and publication policy

Results from the study will be presented at patient information events (e.g., hosted by patient organization Anoiksis, members of which contributed to the design of this study). Additionally, manuscripts about the obtained results (regardless of whether the results are positive, negative, or neutral) will be submitted for publication in peer-reviewed international journals.

## Discussion

Our current study investigates the effects of KE compared with an isocaloric carbohydrate control drink in patients with SSD and BD. To the best of our knowledge, this is the first study to examine the impact of KE in this patient population. Although a few uncontrolled studies suggest beneficial effects of a KD on SSD and BD, dietary interventions can be challenging to study in a controlled setting [44,46,47,95,99,100]. In the context of SSD or BD, adhering to a KD poses an additional challenge, as core symptoms associated with cognitive deficits and negative symptoms like loss of motivation may decrease compliance. The challenging nature of a KD can also lead to selection bias, favoring patients with a lower disease burden and strong social support, thereby limiting generalizability. Importantly, during the acute disease phase, adherence to a strict diet is not feasible. Moreover, it takes several days to weeks to reach sufficient levels of ketosis after starting the KD, rendering this intervention unsuitable to achieve fast ketosis and thus unsuitable as a treatment strategy in the acute disease phase. Finally, psychiatric medications can inhibit ketogenesis, making it hard for patients to reach ketosis on a KD [101]. KE offers an interesting alternative, yielding acute, titratable ketosis. Studies using KE can, therefore, facilitate a more rigorous investigation of the effects of ketone bodies in SSD or BD, while also addressing remaining questions, such as whether achieving ketosis—and at what level—is necessary for symptomatic improvement on a KD. Additionally, if effective, they could provide a viable therapeutic strategy for patients with SSD or BD who struggle with dietary adherence, thereby making ketosis-based interventions more accessible to a diverse patient population.

Our study has several strengths. We consider the broad range of outcomes a strength, because it may inform future trials. Ketone bodies are hypothesized to improve symptoms of SSD/BD through multiple mechanisms. In this pilot study, we focus primarily on their effects on frequently observed electrophysiological abnormalities in SSD and BD (i.e., impaired PPI [53,54], resting-state EEG changes [[73], [74], [75], [76], [77]], and reduced P3B amplitude [73,78,79]). By assessing these electrophysiological outcomes, alongside perceived mood, energy levels, cognitive function and metabolic, oxidative stress, and immune parameters, our current pilot study seeks to understand how ketones may influence brain function in patients with SSD and BD. Ketone bodies may also improve symptoms of SSD or BD through less explored mechanisms, such as the circadian rhythm. Although a single administration of KE may not impact the circadian rhythm, continuously monitoring cortisol and melatonin levels in this study could provide deeper insights into the circadian rhythms of patients with SSD and BD.

Importantly, previous studies often lack consistent measurement of blood ketone levels. In this study, we include sequential measurements of blood ketone levels, providing detailed insights into the dynamics of BHB and after KE ingestion. We hypothesize that the induced hyperketonemia may lead to effects similar to those observed during endogenous ketosis –when ketone bodies are produced by the body itself—based on previous research demonstrating a metabolic competition between ketone bodies and glucose, favoring ketone utilization even in the context of an unchanged diet [27,57].

The randomized AB/BA crossover design of this study is expected to strengthen trial outcomes. In a crossover trial, participants function as their own controls, enhancing both the interpretability of results and the statistical power despite the limited sample size. Moreover, this design reduces interpatient variability in the comparison between groups and the effect of covariates such as participants’ demographic characteristics. Randomization to AB/BA can compensate for test–retest bias and potential carryover effects. By choosing electrophysiological outcome measures (relatively insensitive to test/retest effects), we further reduce bias in this crossover design.

A limitation of this pilot study is the use of a single ingestion of KE, instead of a longer period of supplementation. This limits the outcome measures to parameters with an expected acute response to ketosis. For instance, our current study cannot answer if negative symptoms would improve with KE. We aim to investigate this important question in future studies.

A known limitation of pilot studies investigating novel concepts is the lack of prior data, which prevents the ability to perform an informed power analysis. This, in turn, can weaken the resulting recommendations or conclusions. However, this gap in knowledge is precisely why our current study is necessary. It will provide the data needed to inform a subsequent randomized controlled trial, including a comprehensive power analysis. Another potential limitation is that do not assess whether the participants have a baseline deficit in PPI. It is known that not all patients with SSD and BD exhibit PPI deficits, which could limit the outcomes of our intervention. However, in this study, we will measure the percentage change in PPI after dGK ingestion compared with an isocaloric carbohydrate control drink, allowing each participant to serve as their own control thereby mitigating the effects of this limitation.

There are several biases that need to be considered in this study. The Department of Psychiatry at Amsterdam UMC functions as a regional hospital for acute psychiatric episodes, such as manic episodes or psychosis. The early-episode psychosis ward primarily admits patients who agree to their treatment and are willing to discontinue street drug use. This may introduce selection bias, as it represents only a subset of patients with SSD/BD. Conversely, including a more heterogeneous group could introduce additional confounders and affect the results. In addition, the substantial number of outcome measures in a moderately affected SSD/BD patient population presents a challenge, as it requires several (≤4) hours of intensive testing per test day. This could potentially lead to attrition biases, with more vulnerable patients dropping out of the study. However, we currently successfully finished data acquisition for 9 patients with SSD/BD in our study, without drop-out.

In conclusion, our current study is a first step in exploring the potential benefits of KE to improve symptoms in SSD and BD. By investigating the effects on electrophysiological outcomes, cognitive performance, metabolic, immune, oxidative stress, and circadian rhythm parameters, we aim to deepen our understanding of how ketones influence fundamental brain function related to behavioral and symptomatic manifestations in these patient groups. Our current study is a pilot study aimed at informing future larger-scale research with a longer period of supplementation and longer follow-up evaluating the potential of KE to improve symptoms in SSD and BD. If proven effective, KE could offer a novel and achievable therapeutic approach to modify pathophysiological mechanisms and thereby reduce functional impairments and alleviate the burden of these disorders.

## Data availability

Data described in the manuscript, code book, and analytic code will be made available upon request, pending application and approval.

